## **6. METHODS AND ASSESSMENTS**

### **6.1. Randomisation and Blinding**

Randomisation will be performed using a web-based randomisation system hosted by Singapore Clinical Research Institute (SCRI), in which a randomisation list with randomised permuted blocks will be generated by the trial statistician. Password secured accounts will be assigned to the site personnel who are responsible for the randomisation, where he/she can log into the randomisation system using the Internet.

For the first booster part of the trial randomisation will be stratified by the following criteria:

1. Age (<60, ≥60)
2. Primary vaccine series (BNT162b2 or mRNA-1273)
3. Time from 2nd vaccine dose administered (6-9 months, >9 months)

For the second booster part of the trial randomisation will be stratified by the following criteria:

1. Age (<60, ≥60)
2. Primary vaccine series (BNT162b2 or mRNA-1273)
3. First booster vaccine received (BNT162b2 or mRNA-1273)

Eligible participants will be randomised in equal proportions to each of the study arms that are open for randomisation. Enrolment to a study arm will be discontinued if recommended by DSMB or if the target sample size of 100 in the study arm has been reached. In the scenario where recruitment is discontinued in any of the intervention arms from 1 to 4 at the interim analysis, randomisation to the control arm may continue beyond 100 participants until the target sample size of 100 participants has been reached in the remaining intervention arms.

Allocation concealment will be maintained until the registration and randomisation process have been completed. For Phase A-D of the study, vaccine allocation will be single-blind, i.e. only participants will be blinded. Blinding will be maintained for the participants till their Day-28 Visits (Visit 3).

## **6.2. Contraception and Pregnancy Testing**

For safety reasons, female participants of child-bearing potential will be asked to perform a urine pregnancy test for Phases A-C of the study, and not for Phase D – see trial schedule at section 4 for more information. A negative test result is required to be eligible for the study. At enrolment, all female participants of child-bearing potential will be reminded to use contraception or abstain from sexual intercourse until Visit 3 (Day 28).

## **6.3. Study Visits and Procedures**

### *a. Screening Visit and Procedures*

Participants will be screened based on the inclusion and exclusion criteria stated in Sections 3.3. and 3.4. If participants agree to join the study, they will be asked to sign the informed consent form (ICF) and provide information on relevant medical history. Randomisation will take place at this visit. In Phase A-C of the study blood will be taken from participants for the following clinical labs:

- Full blood count inclusive of differential blood count and platelet count;
- Liver Panel: Albumin, total bilirubin, ALP, ALT;
- Renal Panel: Sodium, potassium, creatinine;
- Cardiology Panel: Creatine kinase, troponin;

The results of the above clinical tests are for comparison with repeat tests at Day 7. Results will not affect eligibility to proceed with randomisation and study vaccination and hence will not be waited for prior to proceeding with Visit 1. These bloods will not be collected at Phase D given the established safety of the vaccines in use in this study as both primary vaccines series and boosters.

Assessment of the participant can occur on the same day as Visit 1, and must be carried out within 28 days prior to the start of the vaccination regimen. The screening visit may occur after five months have elapsed from the second dose of the primary vaccine series. However, the vaccination visit will be within six months per study eligibility criteria.

At the same time, bloods will be collected for research investigations as follows at either screening visit or visit 1:

#### Antibody response assays

To determine the presence and levels of anti-SARS-COV-2 in human sera, a standard ELISA will be used with the whole spike-protein, RBD fragment, or peptides encompassing dominant epitopes of the S and N proteins immobilised in the microplate wells. To identify the repertoire of epitopes induced by the vaccines, a peptide library ELISA will be used. This will provide fine resolution of the antibody responses against

the S-proteins at different time points and help to determine whether there is a fixation of the antibody response to certain epitopes (antigenic sin).

To examine the neutralising capacity of the antibodies in the human sera, two different assays will be performed: the sVNT and the pseudovirus or live-virus assay inhibition.

#### T-cell response assays

Quantitative T-cell responses to the vaccines will be measured using SARS-CoV-2 peptides from spike protein to stimulate the PBMCs isolated from donor's blood. To detect CD8 T-cells, PBMCs will be stimulated with two different peptide pools consisting of MHC-I peptides 8–10 amino acids in length. Negative controls using media and DMSO (~0.5%) will be used as reference. Assays will be performed in duplicates. The cell and peptides will be incubated in ELISpot 96-well plates. After 24 hours, the plates will be washed and assayed for IFN $\gamma$ . To detect CD4 Th1/2 cells, PBMCs will be stimulated with two different peptide pools consisting of MHC-II peptides that are 15 amino acids in length. After 24 hours, the plates will be washed and assayed for IFN $\gamma$  (CD8, Th1) or IL4 (Th2). Spot forming units (SFU) will be measured using IRIS reader (MabTech). Since these assays are done routinely in A\*STAR laboratories and the epitopes have been identified, we do not foresee experimental roadblocks.

#### *b. Study Visits and Procedures*

- Visit 1 (Day 0, 0-28 days after screening)

During the first study visit, participants will undergo a physical examination (if Visit 1 does not occur on the same day as the Screening Visit). Results of clinical blood tests from the screening visit will be reviewed if applicable and available, and results of the urine pregnancy screen from women with child bearing potential. Urine pregnancy test will only be conducted for Phases A-C of the study, and not for Phase D. Eligibility to proceed with study will be confirmed by a study investigator. Research blood would be taken at this visit if it is not performed during screening.

After review the participant will be administered the vaccine and observed for the next 30 min as per clinical practice. The participant will be given a diary to record all the local and general symptoms experienced after receiving the vaccination. Local symptoms may include pain, redness, swelling, bruising, itchiness, muscle ache or movement limitation at the injection site. General symptoms may include headache, fever, nausea, vomiting, sore throat, cough, runny nose, tiredness and red (sore) eyes, as well as symptoms suggestive of COVID-19 infections (e.g. fever, cough and shortness of breath). This diary will cover 7 days post-vaccination and must be returned to the study team when the participant comes for the next visit.

- Visit 2 (Day 7,  $\pm 2$  days)

After physical examination and medical review, blood will be taken from the participant for the laboratory (research and if applicable safety) tests as shown in the trial schedule. The study team will examine the participant's, record vital signs and record any AE or SAEs.

- Visit 3 (Day 28,  $\pm 7$  days)

After physical examination and medical review, blood will be taken from the participant for the laboratory research tests as shown in the trial schedule. The study team will examine the participant's, record vital signs and record any or SAEs. The study participant will be unblinded and vaccination dose recorded in subject's record.

- Visit 4 (Day 180,  $\pm 14$  days)

The subject will report to the clinic for monitoring of vital signs and recording of any SAEs. Blood will be taken from the participant for the laboratory research tests as shown in the trial schedule.

- Final Study Visit (Day 360,  $\pm 14$  days)

The participant will report to the clinic for monitoring of vital signs and recording of any SAEs. Blood will be taken from the participant for the laboratory research tests as shown in the trial schedule. Unless there are any SAEs that need to be followed up closely, the participant will be discharged from the study after this visit.

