| Physical examination                 | X                      | X       | X                  | X                   |                       |                       |
| Vital signs                          | X                      | X       | X                  | X                   | X                     | X                     |
| Pregnancy test                       |                        | X       |                    |                     |                       |                       |
| Medical review                                   | X                      | X       | X                  | X                   |                       |                       |
| COVID-19 infection review            |                        | X       | X                  | X                   | X                     | X                     |
| AE evaluation                        |                        |         | X                  | X                   |                       |                       |
| SAEs, AEs of special interest (e.g. myocarditis, |                        |         |                    |                     |                       |                       |

|                                                        |   |                 |   |   |   |   |
|--------------------------------------------------------|---|-----------------|---|---|---|---|
| pericarditis), medically attended AEs                  |   |                 |   |   |   |   |
| Safety laboratory (Phase A-C only) |   |                 |   |   |   |   |
| Haematology                               | X |                 | X |   |   |   |
| Liver and renal panel                     | X |                 | X |   |   |   |
| Cardiology panel                          | X |                 | X |   |   |   |
| Research laboratory                             |   |                 |   |   |   |   |
| Blood samples for immunogenic analysis    | X | X  | X | X | X | X |

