**Footnotes:**

 Screening visit may be performed on the same day as Visit 1

 Informed consent must be signed prior to initiating any study procedures;

 Randomisation is subjected to vaccine availability;

 Visit 1: third vaccine shot for participant (first and only vaccine administered for the study);

 Physical examination will be done by a qualified study team member or a treating licensed healthcare provider. The physical examination on visit 1 will be conducted during screening prior to vaccination;

 Vital signs include pulse, systolic and diastolic blood pressure, respiratory rate and body temperature prior to vaccination and blood collection;

 For women of child bearing potential a urine pregnancy test will be conducted for Phases A-C of the study, and not for Phase D;

 At each study visit, a review for PCR-confirmed COVID-19 infection will be conducted. In most cases, such information will be available in the participant's HealthHub app. In addition, a review for any positive COVID-19 detected by self-administered Antigen Rapid Test (ART)/supervised self-administered ART/medical professional administered ART will be conducted. For positive results, the category of ART (whether it was self-administered or supervised or administered by a medical professional), the brand of the ART kit used (only if self-administered), and the date of ART positive will be captured;

 All AEs including a list of solicited and other events will be recorded for 7 days after vaccination (see diary version 3.0). Unsolicited AEs will be recorded up to day 28 after vaccination. SAE will be recorded from first vaccination until the end of study period at 12 months. They will be assessed via the listed study procedures, safety laboratory tests, and participant self-recorded diary;

 Safety laboratory bloods will only be monitored during Phases A-C of the study, and not for Phase D

 Haematology tests include full blood count with differential and platelet counts;

 Liver panel includes Albumin, total bilirubin, alkaline phosphatase (ALP), alanine transaminase (ALT); Renal panel includes sodium, potassium and creatinine;

 Cardiology panel include creatine kinase, troponin;

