### **8.5. Blinding**

Only study participants will be blinded to the vaccine allocation. This is to reduce the risk of bias in participant-reported AEs. The study participant will be unblinded at the Day-28 visit (Visit 3) and the vaccination details recorded in the participant's national immunisation record.

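### Participants seen early in the visit windows hand in the diary before 7 days are over, and leave AE evaluation and blinding before Day 28

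*Protocol*

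**What the plan says.** The objectives table in Protocol section 2.2 lists two reactogenicity and safety outcomes with fixed periods: solicited reactions over 7 days after injection and unsolicited AEs over 28 days. Footnote 9 to Table 1 (section 4) repeats both periods, for example "Unsolicited AEs will be recorded up to day 28 after vaccination".

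The visit rules are in Table 1 and section 6.3 b:

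- Visit 2 is Day 7 ±2 days. The diary handed out at vaccination is tied to it: "This diary will cover 7 days post-vaccination and must be returned to the study team when the participant comes for the next visit".
- Visit 3 is Day 28 ±7 days. At this visit "The study participant will be unblinded and vaccination dose recorded". Section 6.1 also ends blinding at attendance of Visit 3.
- Visit 4 is Day 180 ±14 days: "The subject will report to the clinic for monitoring of vital signs and recording of any SAEs".
- The AE evaluation row of Table 1 is marked at Visits 2 and 3 only.

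Section 8.5 gives the reason for blinding participants: "This is to reduce the risk of bias in participant-reported AEs".

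Three further statements bear on the point. Section 2.2 collects serious, special-interest and medically attended events for the whole study. Section 5.1 names self-reporting as one means of AE follow-up. Section 9.1 says that AE monitoring runs only to Visit 2 (Day 7).

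**The concern.** The AE periods are fixed in days after vaccination. Diary return, the last AE evaluation and unblinding are instead tied to visits that may fall before those periods end. A participant who follows every instruction can therefore have less than the stated observation time. Nothing in the protocol closes the gap: there is no later diary return, no contact at Day 28 and no rule holding unblinding until Day 28 has passed.

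Section 11.2 b summarises AEs as the frequency and proportion of participants with an event. Such proportions would be read as 7-day and 28-day incidences, although follow-up differs between participants through booking alone. An event that arises between an early Visit 3 and Day 28 is either missed or reported by someone who already knows the vaccine, which works against the stated reason for blinding.

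This matters somewhat more in Phase D, which has no safety laboratory tests (Table 1, footnote 10) and no DSMB (sections 5.1 and 9.4). There, clinic- and participant-reported events carry more of the safety evidence. Analysis cannot restore data that were not collected, or blinding already lost, so this is a matter of protocol conduct and not of the SAP.

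**Working it through.** The protocol gives no figure of its own to reproduce. The check is arithmetic on its windows, with vaccination on Day 0.

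**Largest shortfall within the rules** (earliest visit = nominal day − window; shortfall = end of AE period − earliest visit)

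| | Solicited (diary) | Unsolicited AEs |
|---|---|---|
| End of period | Day 7 | Day 28 |
| Closing visit | Visit 2, 7 ± 2 = Days 5 to 9 | Visit 3, 28 ± 7 = Days 21 to 35 |
| Earliest visit | 7 − 2 = Day 5 | 28 − 7 = Day 21 |
| Largest shortfall | 7 − 5 = 2 days | 28 − 21 = 7 days |
| Share of period | 2/7 = 29% | 7/28 = 25% |

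The diary figure depends on the day count. If Day 0 is the first diary day, the diary runs over Days 0 to 6. A Day 5 visit then costs Day 6 and the rest of Day 5, so between 1 and 2 days.

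**Next scheduled contact.** Visit 4 is at the earliest on Day 180 − 14 = 166. After a Day 21 Visit 3 that is 166 − 21 = 145 days later.

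**How many participants.** The protocol does not say how visits spread over the windows. The share affected is 0% if every visit falls on or after its nominal day, and 100% if every visit falls before it. As an illustration only, assume an even spread over the allowed days:

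- Visit 2 (5 days allowed, 2 of them early): 2/5 = 40% early. Mean loss (2 + 1)/5 = 0.6 day, and 0.6/7 = 9%.
- Visit 3 (15 days allowed, 7 of them early): 7/15 = 47% early. Mean loss (7 + 6 + 5 + 4 + 3 + 2 + 1)/15 = 28/15 = 1.9 days, and 1.87/28 = 7%.

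Bookings clustered on the nominal day would give smaller figures.

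**What blinding covers.** The earliest unblinding, Day 21, is 21 − 7 = 14 days after the diary period ends. Early unblinding therefore affects only the 28-day period, not the solicited reactions.

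**What is still captured.** Serious, special-interest and medically attended events continue under section 2.2. Reactions in the last diary days can still be recalled and recorded as AEs at Visit 3. Exposed without a scheduled route are diary-format data for the last days, and events between an early Visit 3 and Day 28 that fall outside those three categories.

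**The case against.** The best defence is that the recording periods in footnote 9 are stated in days and are not made conditional on visits. No sentence says that recording of unsolicited AEs stops at an early Visit 3, section 5.1 allows for self-reporting, and the diary document, which is not at hand, may tell early attenders what to do. Symmetric windows around blood draws are common, the outcomes are secondary, and they are only summarised descriptively.

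Part of this stands. The intention to cover 7 and 28 days is clear, and the most important events remain covered. But the instruction to return the diary at Visit 2 is mandatory, and general self-reporting is not a scheduled collection of AEs. The unblinding rule follows attendance in sections 6.1, 6.3 b and 8.5 alike.

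A reader might infer more than the protocol supports:

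- *That all AE collection ends at Visit 3.* Section 2.2 says otherwise for the three categories collected throughout. Their row in Table 1 shows no marks, but a merged cell may have been lost in reading the PDF, so nothing rests on it.
- *That the loss differs between arms because the study team is unblinded.* The windows are the same in every randomised arm, and nothing indicates booking by arm.
- *That an event is both lost and reported unblinded.* For any one event these are alternatives.
- *That 40% and 47% are estimates.* They hold only under the assumed even spread.

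**Conclusion.** The conflict is real for participants seen early, and only for them. The largest shortfall within the rules is 2 of 7 diary days (1 to 2, depending on the day count) and 7 of 28 days of scheduled, blinded AE follow-up. Participants seen on or after Day 7 and Day 28 lose nothing.

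The effect is confined to secondary safety outcomes: diary completeness, and unsolicited AEs that are non-serious, not of special interest and not medically attended. The Day 28 anti-spike endpoint is not affected. The two shortfalls follow directly from the protocol's windows. The number of participants concerned cannot be derived from it, and no imbalance between arms is shown. The point is worth correcting because the remedy is cheap and the AE-period text needs an edit in any case.

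**What to change.** Keep the blood-draw windows and separate AE close-out from them:

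1. Anyone seen at Visit 2 before Day 7 keeps the diary to the end of the 7 days and returns it by photo, by post or at Visit 3. State whether Day 0 is the first diary day.
2. Anyone seen at Visit 3 before Day 28 gives a brief remote AE report at Day 28.
3. Unblind these participants only after that report. Section 8.5 places the entry in the national immunisation record at the same visit, so its wording has to be aligned.
4. In the same edit, reconcile section 9.1 (AE monitoring to Visit 2, Day 7) with the 28-day period in section 2.2, footnote 9 and section 5.1. Also repair the Visit 3 sentence in section 6.3 b, where a word appears to be missing before the mention of SAEs.

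The cost is protocol wording, a short remote contact for early attenders, and unblinding delayed by at most 28 − 21 = 7 days for them.

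One-sided visit windows (Days 7 to 9 and Days 28 to 35) would also close the gap, but they are a trade-off. Visit 3 supplies the primary blood sample. Under an even spread its mean day would move from 28 to (28 + 35)/2 = 31.5, and the schedule would differ from that of the 150 participants enrolled in Phases A to C. The remote report avoids this.

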|                                                                                                                                                                                                                                                                                                                                                                                                                | Changes from baseline in laboratory safety measures (Only for Phase A-C)                                                                                                                                                                                                                                            | 7 days after injection  |
|                                                                                                                                                                                                                                                                                                                                                                                                                | Unsolicited adverse events (AEs)                                                                                                                                                                                                                                                                                    | 28 days after injection |
|                                                                                                                                                                                                                                                                                                                                                                                                                | Serious adverse events (SAEs), AEs of special interest (e.g. myocarditis, pericarditis), medically attended AEs                                                                                                                                                                                                     | Throughout the study    |

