COVID-19 vaccines used in the study may have been granted full or interim authorisation (under the Pandemic Special Access Route, PSAR) by the Health Sciences Authority (HSA), have been authorised via the Special Access Route (SAR) for vaccines as part of the Emergency Use List (EUL) of the World Health Organization (WHO), or be under clinical development. BNT162b2, mRNA-1273 were authorised in Singapore under the PSAR, and on 3 Feb, HSA granted interim authorisation for Novavax's vaccine-manufactured under the name Nuvaxovid under PSAR. Nuvaxovid became the first non-mRNA vaccine accepted as an alternative for a boost vaccination in Singapore. Comirnaty Bivalent (Original/Omicron BA.4/5) and Moderna/Spikevax Bivalent (Original/Omicron BA.1) were authorised in Singapore under the PSAR on 11 Oct 2022 and 14 Sept 2022 respectively for use as a booster vaccine.

The non-mRNA vaccine COVAXIN® (Bharat Biotech) was approved by the World Health Organization (WHO) under the Emergency Use Listing (EUL) procedure on 3 Nov 2021 for use in two doses for primary vaccination and is available in Singapore via the SAR. The booster is not approved in the EUL.

Participants will be enrolled at the NCID research clinic. Participants will be blinded to the vaccine allocation (study team will not be blinded) to reduce the risk of bias in self-reported AEs. Participants will receive the blinded vaccination on study day 0 / visit 1. Participants will be observed for 30 minutes in the clinic after vaccination as per standard clinical practice. Participants will be monitored and followed up for AEs at Day 28 and SAEs throughout the study by physical examinations, laboratory tests and self-reporting. Blood samples will also be taken during screening or day 0, and at the follow-up visits at days 7, 28, 180, 360 post-enrolment for evaluation of immunogenicity and/or safety. Any missed follow-up visits by participants will not be considered a protocol deviation as it is beyond the control of the study team if a participant does not turn up for a follow-up visit, especially in a large-scale study.

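### AEs of special interest and medically attended AEs are a whole-study outcome in Section 2.2, but footnote 9, Section 5.1 and the Day 180 and Day 360 visit text name only SAEs after Day 28

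*Protocol*

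**What the plan says.** The outcome table in Section 2.2 lists, for Phases A to D, a secondary safety outcome with three components: "Serious adverse events (SAEs), AEs of special interest (e.g. myocarditis, pericarditis), medically attended AEs". Its time frame is "Throughout the study", so it runs to Day 360.

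Four places say what is recorded over the longer term, and each carries only SAEs past Day 28:

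- Section 6.3 b, Visit 4 (Day 180): "The subject will report to the clinic for monitoring of vital signs and recording of any SAEs".
- Section 6.3 b, Final Study Visit (Day 360): "The participant will report to the clinic for monitoring of vital signs and recording of any SAEs".
- Section 4, footnote 9 to Table 1: "Unsolicited AEs will be recorded up to day 28 after vaccination", and then "SAE will be recorded from first vaccination until the end of study period at 12 months".
- Section 5.1: "Participants will be monitored and followed up for AEs at Day 28 and SAEs throughout the study".

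Table 1 also has its own row for the three classes, beginning "SAEs, AEs of special interest (e.g. myocarditis". The row breaks across a page, and no visit marks can be read in it in the extracted text.

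**The concern.** Up to Day 28, AESIs and medically attended AEs are covered by the general collection of unsolicited AEs. After that they depend on being named, and the text for the two late visits does not name them. Staff working from Section 6.3 and footnote 9 would have no written instruction to ask at Day 180 or Day 360 about, say, an outpatient consultation that met no seriousness criterion.

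At stake is how complete two of the three components of a declared safety outcome would be. If late events are not asked about, a low count cannot be told apart from a low rate. No analysis plan can recover events that nobody asked about, so the matter has to be settled in the protocol. The primary endpoint is not affected.

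**Working it through.** The plan gives no figure to reproduce here. The check sets the passages side by side and then measures the affected window.

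**Step 1. What each place provides for after Day 28**

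| Place | SAEs | AESIs and medically attended AEs |
|---|---|---|
| Section 2.2, outcome table | whole study | whole study |
| Table 1, row for the three classes | marks unreadable | marks unreadable |
| Table 1, AE evaluation and medical review rows | last marked at Visit 3 | last marked at Visit 3 |
| Footnote 9 | to 12 months | not named |
| Section 5.1 | whole study | not named |
| Section 6.3 b, Day 180 | recorded | not named |
| Section 6.3 b, Day 360 | recorded | not named |
| Section 9.4, Phase D monitoring | named | not named (the list is introduced as what monitoring will include, so it need not be complete) |

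**Step 2. How the Table 1 row can be read.** SAEs share that row and are recorded to Day 360 according to footnote 9 and Section 6.3. The blank cells therefore look like marks lost in extraction and are no evidence that nothing is collected. There are two cases:

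- If the row is marked at Visit 4 and the Final Visit, the schedule agrees with Section 2.2 but disagrees with footnote 9, Section 5.1 and the visit text.
- If it is not marked there, nothing in the protocol prompts collection of the two classes after Day 28.

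The passages need reconciling in both cases.

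**Step 3. Which events are affected.** Ordinary unsolicited AEs are meant to stop at Day 28 under both Section 2.2 and footnote 9, so they are outside this point. Events that meet a seriousness criterion in Section 9.3, including the medically important event criterion, are recorded as SAEs throughout. COVID-19 infection has its own review at every visit. What remains is non-serious AESIs and non-serious medically attended AEs.

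**Step 4. Length of the window.** The inputs are the nominal visit days and visit windows in Table 1.

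- Nominal: 360 − 28 = 332 days, and 332/360 = 0.922.
- Visit 3 at its latest (Day 35) and Final Visit at its earliest (Day 346): (346 − 35)/346 = 311/346 = 0.899.
- Visit 3 at its earliest (Day 21) and Final Visit at its latest (Day 374): (374 − 21)/374 = 353/374 = 0.944.

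About 90% to 94% of the stated window has no written recording step for these two classes outside the unreadable row. This is a proportion of time, not of events.

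**A neighbouring inconsistency.** Section 9.1 ends general AE monitoring at Visit 2 (Day 7), whereas footnote 9 and Section 5.1 go to Day 28. It does not change the result above, but the same amendment could settle it.

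**The case against.** The strongest case against is that the visit text is not a complete list of what happens at a visit. For Day 180 and Day 360, Section 6.3 mentions only vital signs, SAEs and blood samples. It leaves out the COVID-19 infection review, although Table 1 marks that review at both visits and footnote 8 requires it at each one. An item missing from Section 6.3 may therefore still be collected. Table 1 also keeps the row for the three classes apart from the AE evaluation row, which suggests a longer schedule that matches Section 2.2. This stands, and it is why the documents do not show that these events go uncollected. It does not remove the contradiction, because footnote 9 and Section 5.1 set out follow-up periods by event class and also carry only SAEs past Day 28.

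A second objection is that the AESIs the protocol names, myocarditis and pericarditis, could often be classed as medically important and so be recorded as SAEs. That stands in part. It depends on case-by-case judgement, and it does not cover medically attended AEs as a class.

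A reader might infer more than the documents support in three ways:

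- *That about nine in ten events would go unrecorded.* This needs a constant event rate and no capture at all after Day 28. The protocol gives no event rate, and the unreadable row leaves capture open.
- *That Phase D is worse off because it has no DSMB and no safety bloods.* In Phases A to C the bloods were scheduled only at screening and Day 7, and the planned DSMB review used data to Day 28 from the first 10 participants per intervention arm. Neither was a planned source for these events between Day 28 and Day 360.
- *That incomplete counts would be reported as whole-study rates.* Section 11.2 b specifies summaries of AEs, SAEs and Grade 3 and 4 AEs. It does not say how AESIs or medically attended AEs would be presented, and the analysis plan is not at hand.

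**Conclusion.** The protocol contradicts itself on the follow-up of two of the three components of a secondary safety outcome. Section 2.2 follows them for the whole study; footnote 9, Section 5.1 and both late-visit descriptions carry only SAEs past Day 28. As the text stands, non-serious AESIs and medically attended AEs have no stated recording step for 332 of 360 days and may be under-ascertained.

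This rests on reading footnote 9, Section 5.1 and Section 6.3 as written, and on the marks in the Table 1 row being unknown. If that row is marked at Day 180 and Day 360, what remains is conflicting instructions within the protocol, with a risk of uneven collection. The number of events missed cannot be estimated in either case. The correction is worth making because it is cheap and acts on data that cannot be recovered at analysis.

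**What to change.** Reconcile the passages in one of two ways.

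1. **Collect for the whole study, as Section 2.2 states.** In the Visit 4 and Final Visit text of Section 6.3 b, extend the recording of SAEs to SAEs, AESIs and medically attended AEs since the last visit. In footnote 9 and Section 5.1, replace the SAE-only wording for follow-up beyond Day 28 with the same three classes. Check that the Table 1 row is marked at Visit 4 and the Final Visit, and add the marks only if they are absent.
2. **If these events are not collected after Day 28,** restate the time frame of the AESI and medically attended AE components in Section 2.2 as the period in which they are actually collected, and leave SAEs at whole-study follow-up.

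The first option costs a wording amendment plus one question and one CRF line at two visits that already take place; it adds no visit or test. The second costs a wording change only, but gives up longer-term information on non-serious events in these two classes.
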